### Monitoring

A trial management committee comprising of the principal investigators, supported by the co-investigators from the other participating sites, was formed. The trial management committee is responsible for the day-to-day running and management of the trial. In order to standardize the research procedures, the researchers, physicians, and nurses are trained in standard clinical practice. A standard case report form is developed for every participant. Obtained data is stored strictly. Data will be analyzed by a statistician after the removal of any participant identifier information. Data are analyzed at the completion of this study.

## Discussion

In the present study, we would conduct a prospective, multi-centered, double-blinded, randomized, placebo-controlled superiority clinical trial named HDVCOS. Its aim is to testify to the efficacy and safety of high-dose vitamin C in the treatment of sepsis.

The clinical clue of the supplement of vitamin C in critical illnesses (such as trauma, sepsis, and hemorrhagic shock) has been confirmed for a long time. Severe vitamin C deficiency (plasma concentrations < 11 μmol/L) is commonly seen in nearly 40% patients with sepsis (19). Vitamin C deficiency was reported to be closely related to poor prognosis (20). The reason may be that vitamin C exerts many important functions in our physiological activity: (1) directly erasing reactive oxidative species (ROS); (2) acting as a key cofactor for the biosynthesis of endogenous catecholamines, vasopressin, and cortisol; and (3) functioning as an immune enhancer (21). In recent years, even though two clinical trials separately investigate the effect of intravenous vitamin C on sepsis (15, 16), the conclusion is still elusive. The reason may be the relatively low participants number (*N* = 167 and *N* = 124, separately) and the undefined optimal vitamin C dose and plasma level. Recently, the results of a large multi-center randomized trial were just published and the results indicated no benefit of vitamin C in adults with sepsis (22). However, Asian people were not included in this study. Moreover, the time interval between established diagnosis of sepsis and the application of vitamin C was not provided, which is important to evaluate the effect of vitamin C. Finally, the plasma vitamin C level during and after infusion in this study was not indicated. It was not sure whether the plasma vitamin C concentration was enough for a septic adult. None of the studies to date have obtained this important information either. In our study, plasma vitamin C concentration is measured continuously within the first 7 days, and the outcome will provide important information on this aspect.

In this trial, we will give the vitamin C in a way of sustained injection (200 mg/kg/24 h, 1 g/h) for 4 days. Other published studies (12, 15, 22) used the same dosage of vitamin C (200 mg/kg/24 h) for 4 days in total, but they gave vitamin C in a bolus injection way. According to the study by De Grooth et al. (23), a sustained injection of 10-g vitamin C for 48 h led to a sustained level of vitamin C approximately five times above the normal level, which might be more helpful to prevent hypovitaminosis than bolus injection. In our study, we will test the plasma vitamin C concentration with high-performance liquid chromatography on days 0, 3, 4, and 7, and the result may provide information on optimal drug delivery ways and plasma concentrations.

The most concern of high-dose vitamin C safety is its potential harm to renal function and the formation of kidney stones (24). A previous case report showed that high-dose oral intake of vitamin C for 6 years led to high urine oxalate excretion and ureteral stone formation in a 9-year-old child. However, there was no reported case of renal stone as an adverse event of short-term intravenous usage of high-dose vitamin C (25). Furthermore, no adverse event was reported in critical illness clinical trials. Anyway, the renal function change of enrolled patients should receive timely evaluation. Patients with a history of renal oxalate stones will not be enrolled in the study.

There are some limitations to this study. First, the rapid degradation quality of vitamin C and the inconvenient availability of high-performance liquid chromatography could influence the accuracy of plasma vitamin C concentration detection. Second, patients with kidney stones were excluded from the trial, which may exclude most of the patients with sepsis originating from the urinary tract.

Vitamin C is a cheap and easily available agent. We expect that the results of this study will provide a scientific rationale for the use of high-dose vitamin C in improving the prognosis of patients with sepsis.

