## Methods and analysis

### Study design

We have designed the High-Dose Vitamin C on Sepsis (HDVCOS) study as a prospective, multi-centered, double-blinded, randomized, placebo-controlled, superior clinical trial. Till now, five centers in China have been involved. The trial protocol is approved by the Clinical Trail Ethics Committee of Ruijin Hospital of Shanghai Jiao Tong University School of Medicine (2018-145) and all the participating centers. This trial has been registered in the Chinese Clinical Trial Registry (ChiCTR1800017633). A total of 620 participants diagnosed with sepsis that satisfy the eligibility criteria will be randomized at a ratio of 1:1 to receive treatment with a high-dose intravenous injection of vitamin C (200 mg/kg/24 h) or placebo (saline) for 4 days.

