#### Exclusion criteria

The exclusion criteria were as follows:

1.Patients or their surrogate refuse to receive cardiovascular (vasopressor agent), respiratory (mechanical ventilation), or renal (renal replacement therapy) supports during the treatment period.2.Pregnant patients or in lactation.3.Patients with poorly controlled chronic organ failure, defined as: (1) chronic cardiovascular dysfunction requiring long-term mechanical hemodynamic support or inotropes support, (2) chronic obstructive pulmonary disease requiring home oxygen, (3) chronic hepatic dysfunction classified as Child-Pugh C, (4) chronic renal disease with an eGFR < 60 ml/min/1.73 m^2^ or serum creatinine >150 μmol/L.4.Patients allergic to vitamin C.5.Patients who are participating or have participated in other investigational studies.6.Patients who weigh more than 100 kg.7.Patients with kidney stone.

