#### Regular treatment

The sepsis 3.0 guideline will be followed for the regular management of patients with sepsis (17). This includes fluid resuscitation, antibiotics, vasopressor titration, mechanical ventilation and ventilator weaning strategies, blood transfusion, nutrition, renal replacement therapy, delirium management, and glycemic control.

Group 1: Vitamin C group

The vitamin C (Brilliant, China) with a dose of 200 mg/kg/24 h is given by continuous injection through the central venous with a speed of 5 ml/h for 4 days.

Group 2: NS group

The.9% NS (Baxter, China) with the same volume as corresponding vitamin C is given by continuous injection through the central venous with a speed of 5 ml/h for 4 days.

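### The study drug's stated amount (200 mg/kg/24 h), rate (1 g/h) and continuous delivery cannot all hold for any eligible patient

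*Protocol article*

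**What the plan says.** The protocol article describes the vitamin C regimen in several places.

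- **Study design** (and the abstract, to the same effect): "high-dose intravenous injection of vitamin C (200 mg/kg/24 h) or placebo (saline) for 4 days". No rate in g/h is given.
- **Regular treatment, Group 1**: vitamin C "with a dose of 200 mg/kg/24 h is given by continuous injection through the central venous with a speed of 5 ml/h for 4 days". No drug concentration is given.
- **Regular treatment, Group 2**: saline "with the same volume as corresponding vitamin C is given by continuous injection", also at 5 ml/h for 4 days.
- **Discussion**: "In this trial, we will give the vitamin C in a way of sustained injection (200 mg/kg/24 h, 1 g/h) for 4 days". This is the only place where 1 g/h appears. The next sentence contrasts this delivery with bolus dosing in earlier studies that are said to have used the same dosage.
- **Exclusion criteria, item 6**: "Patients who weigh more than 100 kg".

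The article states no reference weight, dose cap or number of infusion hours per day that would link a fixed 1 g/h to a dose per kilogram.

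**The concern.** A dose per kilogram per 24 h given continuously implies an hourly rate that rises with body weight. A fixed 1 g/h does not depend on weight. The Discussion puts the two side by side as one regimen, so they can agree at one weight at most, and the weight limit decides whether any eligible patient has that weight.

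This concerns the experimental treatment itself, so three things depend on it.

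- **Safety.** The Discussion names renal harm and stone formation as the main worry with high-dose vitamin C. The daily amount should be unambiguous.
- **Plasma levels.** Vitamin C concentration and its relation to outcomes is a secondary outcome, with samples on days 0, 3, 4 and 7. A sample on day 3 or 4 means one thing if the infusion is running and another if it stopped hours before.
- **Comparison with earlier trials.** The Discussion argues that the dosage is the same and only the mode of delivery differs. That argument needs both the amount and the duration to be clear. The planned per-protocol comparison likewise presupposes a single defined regimen.

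**Working it through.** **Inputs**

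| Input | Value | Source |
|---|---|---|
| Daily dose | 200 mg/kg/24 h | Abstract, Study design, Regular treatment, Discussion |
| Rate by mass | 1 g/h | Discussion only |
| Rate by volume | 5 ml/h | Regular treatment |
| Delivery | continuous or sustained, 4 days | Regular treatment, Discussion |
| Maximum eligible weight | 100 kg | Exclusion criteria, item 6 |
| Weights below 100 kg | 50, 60, 70, 80 kg | assumed, for illustration |

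**Step 1. Can 1 g/h be reproduced from the daily dose?** Over 24 h, 1 g/h is 1 × 24 = 24 g. The weight at which this equals 200 mg/kg is 24 g ÷ 0.2 g/kg = 120 kg. That is above the 100 kg limit. At the limit the weight-based dose is 0.2 × 100 = 20 g per 24 h, or 20 ÷ 24 = 0.833 g/h, the highest rate that any eligible patient can have. The stated 1 g/h is therefore not reproduced for anyone in the trial. This step uses only figures from the article.

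**Step 2. The two readings by weight.** The formulas are:

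- weight-based rate = 0.2 × weight ÷ 24
- 1 g/h for 24 h, per kg = 24,000 ÷ weight
- ratio to the weight-based dose = 120 ÷ weight
- hours to deliver the daily dose at 1 g/h = 0.2 × weight

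| Weight | 200 mg/kg/24 h, as g/24 h | As g/h | 1 g/h for 24 h, as mg/kg/24 h | Ratio | Hours per day at 1 g/h until dose used up |
|---|---|---|---|---|---|
| 50 kg | 10 | 0.417 | 480 | 2.4 | 10 |
| 60 kg | 12 | 0.500 | 400 | 2.0 | 12 |
| 70 kg | 14 | 0.583 | 343 | 1.71 | 14 |
| 80 kg | 16 | 0.667 | 300 | 1.5 | 16 |
| 100 kg (limit) | 20 | 0.833 | 240 | 1.2 | 20 |
| 120 kg (not eligible) | 24 | 1.000 | 200 | 1.0 | 24 |

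Over 4 days, 1 g/h round the clock gives 96 g. The weight-based dose gives 4 × 14 = 56 g at 70 kg and 4 × 20 = 80 g at 100 kg.

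**Step 3. Does 5 ml/h settle it?** Continuous 5 ml/h is 5 × 24 = 120 ml per 24 h. Three schemes fit that pump rate:

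- 1 g/h for 24 h needs 1,000 mg ÷ 5 ml = 200 mg/ml for everyone.
- 200 mg/kg spread over 24 h needs a concentration that varies with weight: 83.3 mg/ml at 50 kg (10,000 ÷ 120) and 166.7 mg/ml at 100 kg (20,000 ÷ 120).
- A fixed 200 mg/ml with a weight-dependent volume needs 1 ml per kg per day: 50 ml over 10 h at 50 kg and 100 ml over 20 h at 100 kg.

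The volume-matched placebo is compatible with all three. The 200 mg/ml is derived here and is not stated in the article. So 5 ml/h does not decide between the readings.

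**Step 4. What each reading gives up.** Keeping 1 g/h and continuous delivery gives up 200 mg/kg/24 h. Keeping 200 mg/kg/24 h and continuous delivery gives up 1 g/h. Keeping 200 mg/kg/24 h and 1 g/h gives up continuous delivery, leaving 4 to 14 h each day without infusion at 100 to 50 kg.

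**The case against.** The strongest reply is that 1 g/h may be just a pump rate and 200 mg/kg the daily total. Under that reading every eligible patient receives exactly the weight-based amount, and the daily dose always fits within 24 h. The intervention section lends it some support: if the saline volume follows the patient's own vitamin C volume at a fixed 5 ml/h, the duration would vary with weight. This part stands. A reader might infer that 1 g/h means too large a daily amount for every eligible patient. The article does not support that, because the ratio may be 1.0 at every weight. What remains even then is a conflict over duration: infusions of 10 to 20 h a day do not fit delivery described as continuous and sustained, although they would still not be boluses.

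A reader might also infer that 5 ml/h is compatible with weight-based dosing only if the concentration changes with weight. It is not so, as Step 3 shows. Nor is the missing concentration a defect, since a condensed article may leave preparation detail to the full protocol.

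It is also fair to say that 1 g/h appears once, in a parenthesis in the Discussion, while the abstract and both methods sections give 200 mg/kg/24 h consistently. An unblinded nurse prepares the drug, staff are trained to standardise procedures, and nothing shows that sites dose from the Discussion. The figure may be a publication slip. That limits what can be said about consequences, but it does not remove the inconsistency: the sentence describes this trial's own treatment, and two of its figures conflict under the delivery that the article describes.

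**Conclusion.** The point holds as an internal inconsistency between daily amount, hourly rate and continuous delivery. For patients up to 100 kg the three cannot all be true, and this conclusion needs no assumed weight.

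The size depends on the reading. The daily amount under 1 g/h ranges from 1.0 times the weight-based dose (rate used only until the dose is delivered) to between 1.2 times at 100 kg and 2.4 times at an assumed 50 kg (rate run for 24 h). Under the first of these the discrepancy moves to duration, at 10 to 20 h per day. Rounding does not explain it, since the closest any eligible patient comes to 1 g/h is 0.833 g/h.

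A reader might go further and infer that patients were overdosed or that sites treated patients differently. The article does not show either. This review does not say which figure is right.

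**What to change.** The sponsor should set the Exclusion criteria (weight limit), the Regular treatment section and the Discussion against the preparation instruction that the drug-preparing nurse uses. One arithmetically consistent statement of amount, rate and daily infusion duration should result, and whichever text is wrong should be corrected. The sponsor should then check preparation records to confirm that all sites followed the same regimen. If they did, the matter is a correction to the text. If they did not, the differences need to be known before the plasma concentrations and the per-protocol comparison are interpreted.

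The cost is a protocol clarification, a memo to sites and a records check. None of this changes the design, the sample size or the primary analysis. The records check should be done by staff who are already unblinded, so that the blind is kept.

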## Trial status

The trial start date was 1 August 2019. Considering the influence of COVID-19, the anticipated recruitment end date will be 31 December 2023.

## Ethics statement

The studies involving human participants were reviewed and approved by Clinical Trail Ethics Committee of Ruijin Hospital of Shanghai Jiao Tong University School of Medicine. The patients/participants provided their written informed consent to participate in this study.
